**Time and Events Schedule for Protocol**

| Procedure                                            | Screening / Pre-Treatment Visit | During Treatment Visits a
[Induction and Re-Induction]:
d 1 (W1),
d 22 (W4),
d 43 (W7),
d 64 (W10)
(+/- 7 days) | During Re-Staging-Visits b
(Week 12/24/
36/48) | End of Treatment Visit X (10 weeks after last administration) | FU-Phase m
(every 3 months) | Protocol Section  |
|------------------------------------------------------|---------------------------------|----------------------------------------------------------------------------------------------------------------------------------------------|-----------------------------------------------------------------|---------------------------------------------------------------|-------------------------------------------|-------------------|
| Eligibility Assessments                       |                                 |                                                                                                                                              |                                                                 |                                                               |                                           |                   |
| Tumour Biopsy for b-raf mutation status j | X                               |                                                                                                                                              |                                                                 |                                                               |                                           |                   |
| Informed Consent                                     | X                               |                                                                                                                                              |                                                                 |                                                               |                                           | 13.3              |
| Inclusion/Exclusion Criteria                         | X                               |                                                                                                                                              |                                                                 |                                                               |                                           | 4.1 + 4.2         |
| Medical History                                      | X                               |                                                                                                                                              |                                                                 |                                                               |                                           | 6.1.1.1           |
| Safety Assessments                            |                                 |                                                                                                                                              |                                                                 |                                                               |                                           |                   |
| Physical Examination                                 | X                               | X                                                                                                                                            | X                                                               | X                                                             | X                                         | 6.1.1.1 - 6.1.1.4 |
| Vital Signs c                             | X                               | X                                                                                                                                            | X                                                               | X                                                             |                                           | 6.1.1.1 - 6.1.1.4 |
| ECOG Performance Status                              | X                               | X                                                                                                                                            | X                                                               | X                                                             |                                           | 6.1.1.1 - 6.1.1.4 |
| ECG                                                  | X                               | (X) i                                                                                                                             | X                                                               |                                                               |                                           |                   |
| Assessment of Signs and Symptoms                     | X                               | X                                                                                                                                            | X                                                               | X                                                             |                                           | 6.1.1.1; 6.1.1.4  |
| Adverse Events Assessment                            |                                 | X                                                                                                                                            | X                                                               |                                                               |                                           | 6.2+ 8.           |
| Laboratory Tests d, e                     | X                               | X                                                                                                                                            | X                                                               | X                                                             |                                           | 6.1.1.1 - 6.1.1.4 |
| Urinalysis (urine dipstick for protein)              | X                               | X                                                                                                                                            | X                                                               |                                                               |                                           | 6.1.1.2; 6.1.1.3  |
| Urine β-HCG-Pregnancy Test f              | X                               |                                                                                                                                              | X                                                               |                                                               |                                           | 6.1.1.1; 6.1.1.2  |

**Time and Events Schedule for Protocol**

| Procedure                                                                         | Screening / Pre-Treatment Visit | During Treatment Visits a
[Induction and Re-Induction]:
d 1 (W1),
d 22 (W4),
d 43 (W7),
d 64 (W10)
(+/- 7 days) | During Re-Staging-Visits b
(Week 12/24/
36/48) | End of Treatment Visit X (10 weeks after last administration) | FU-Phase m
(every 3 months) | Protocol Section           |
|-----------------------------------------------------------------------------------|---------------------------------|----------------------------------------------------------------------------------------------------------------------------------------------|-----------------------------------------------------------------|---------------------------------------------------------------|-------------------------------------------|----------------------------|
| Efficacy Assessments (according to irRC and RECIST criteria, respectively) |                                 |                                                                                                                                              |                                                                 |                                                               |                                           |                            |
| MRT/CT-brain g, h                                                      | X                               |                                                                                                                                              | X                                                               |                                                               |                                           | 6.1.1.1; 6.1.1.3;
6.3.2 |
| MRT/CT-thorax/abdomen/pelvis g, h                                      | X                               |                                                                                                                                              | X                                                               |                                                               |                                           | 6.1.1.1; 6.1.1.3;
6.3.2 |
| Clinical Drug Supplies                                                     |                                 |                                                                                                                                              |                                                                 |                                                               |                                           |                            |
| Dispense Study Treatment                                                          |                                 | X                                                                                                                                            |                                                                 |                                                               |                                           | 5.                         |
| Survival assessment                                                               |                                 | X                                                                                                                                            | X                                                               | X                                                             | X                                         | 6.1.1.5                    |
| Translational Research Programm
(separate informed consent)            |                                 |                                                                                                                                              |                                                                 |                                                               |                                           |                            |
| Whole venous blood 20ml                                                           | X                               |                                                                                                                                              | X n                                                  |                                                               |                                           | 6.4                        |
| EDTA "full blood" 2 ml                                                            | X i                  |                                                                                                                                              |                                                                 |                                                               |                                           | 6.4                        |
| Tissue biopsy (an additional fresh biopsy is optional)                            | X j                  |                                                                                                                                              |                                                                 |                                                               |                                           | 6.4                        |

a/b Includes visits during induction and re-induction periods of the study.

c Blood pressure every 30 minutes during ipilimumab + 1 hour following completion of infusion (Sect. 6.2.1.2)

d All period laboratory samples must be collected within a window of up to 3 days before administration of ipilimumab

e TSH, free T4 at baseline, Visit 2, 3, 4, 5. **The assessment of TSH at baseline and before each treatment is mandatory. The TSH level must be available to the investigator prior to each administration.**

f A pregnancy test must be conducted and a negative result must be confirmed before the first administration of ipilimumab and after week 12

g within 6 weeks before start of therapy.

h The same method of assessment must be used throughout the trial to ensure comparability

i EDTA "full blood" for SNP, HLA-A2 typing once at the beginning of the study or any other time point of the study

j if not available until then, for b-raf status of tumor biopsy

k laboratory parameters: evaluation for LDH and S-100 should be performed at baseline, visit 2,3,5 (week 4, 7, 12)

l at baseline and week 12, if clinically indicated (evident of myocarditis e.g. dyspnoea, functional insufficiency) to be done before each treatment

m FU-phase is defined after initial progress and non-eligibility for re-induction. For each subject, survival status (alive/dead and date) will be collected every 3 mths until 1 year post the subjects's first treatment dose.

n Serum and plasma only at screening and at week 12

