**Secondary Endpoint (s)**

- All adverse events  $\geq$  Grade 3 according to CTCAE, Version 4.0 criteria, that are definitely, probably, or possibly related to the administration of the investigational agents will be assessed.
- Overall response rate (PR+CR) according to immune-related response Criteria (ir-RC) at any time in the study.
- Disease control rate irDCR (rate of CR or PR or SD) according to immune-related response Criteria (ir-RC) at any time in the study.
- Overall response rate (PR+CR) according to RECIST criteria at any time in the study.
- Disease control rate (CR or PR or SD) according to RECIST criteria at any time in the study.
- Progression free survival rate at 6 months, PFS is defined as the time from the first study treatment date until the first documented tumor progression date (as defined by immune related response criteria) or date of death, whichever occurs first.
- Overall survival
- Clinical efficacy parameter (1-year OS, ORR, DCR, PFS at 6 months) according to b-raf mutational status of tumor (b-raf V600E yes versus no), brain metastases, LDH and HLA-A2

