This trial is designed in light of the high unmet medical need in the treatment of metastatic melanoma and the promising clinical results derived from trials with ipilimumab. Various phase II clinical studies using ipilimumab in unresectable stage III-IV have been conducted. Results of the first pivotal phase III study MDX010-20 were presented at ASCO 2010 (O'Day et al., JCO 2010) and published in parallel by Hodi et al. (NEJM, 2010). In the second ongoing phase III trial CA184-024, a different dose and treatment scheme is currently tested in the first-line setting. Results are expected at the end of 2010.

However, due to strictly defined inclusion and exclusion criteria in phase III trials, results of registrational trials might not answer all questions regarding safety and efficacy of ipilimumab in all advanced melanoma patient cohorts seen in daily routine. E.g. on one hand, in MDX010-20 trial, only patients positive for HLA-A2 could be enrolled (since patients were randomized in a double-blind fashion in a 1:3:1 ratio to receive HLA2-restricted melanoma gp 100 peptide vaccine monotherapy, MDX-010 in combination with melanoma gp100 peptide vaccine, or MDX-010 monotherapy.) In the second currently ongoing phase III study 184-024 patients were not restricted to HLAA2+ haplotype. However, a different patient group was enrolled (first line situation) and another dosing and treatment scheme was tested (combination with DTIC; ipilimumab 10mg/kg and maintenance period following induction phase for patients who benefitted from ipilimumab). Patients with primary mucosal melanoma were excluded in CA184-024 study; patients with primary ocular melanoma were excluded in both Mdx010-20 as well as in CA184-024.

A large clinical phase II trial is proposed to treat broad range of metastatic melanoma patients who have failed at least one systemic treatment regimen in advanced, non-resectable melanoma. This study aims to gain more information about efficacy and safety of ipilimumab in a broad range of clinically relevant pretreated patient cohorts seen in daily routine, neither addressed in MDX-010-20 study nor in CA184-024. Enrollment will not be restricted to any specific HLA subtype and patients with uveal or ocular melanoma as well as cutaneous

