#### *Sample processing for plasma:*

- ◆ Draw tubes of 10 ml whole blood in Corvac Plasma Separator Tube (Sherwood Medical, St.Louis, MO). Tube contains lithium-heparin
- ◆ Allow for plasma separation for 1 hour at room temperature.

- ◆ Divide plasma in at least 8 aliquots (approximately 1 ml each) in 1.8 ml cryotubes (Nunc or equivalent).

In context of this study, **2 ml EDTA “full blood”** for HLA-typing and single nucleotide polymorphism (SNP) analysis will be collected once at the beginning of the study or any other time point of the study. Full blood can be stored without further processing at -70°C.

- ◆ **All samples** will be store at -70 °C until collection via centr al laboratory at

Labor der Universitäts-Hautklinik Essen

z.H. [name]

[name]

[name]

[contact]

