#### 9.5. Statistical analysis

The primary endpoint, one year survival rate, is based on the ITT population. As a simple rate, it will be calculated as the number of patients being still alive 12 months after their first administration of the study treatment divided by the number of patients having received at least one administration of the study treatment. Only subjects known to be alive at 1 year will be included in the numerator. As a time to event variable, it will be derived from the Kaplan-Meier curve. In this case missing data will be censored at the last contact. See below for further details.

All other analyses will have exploratory character. Results will be presented overall and per cohort/subgroup:

- (1) cutaneous vs uveal vs. mucosal melanoma
- (2) - LDH < 2 UNL versus LDH ≥ 2 UNL
- (3) - status brain mets versus no brain mets in medical history
- (4) - status Braf mutation positive versus. Braf mutation negative
- (5) - HLA-A2 positive versus HLA-A2 negative

Demographic and baseline characteristics will be tabulated for all treated subjects. For categorical variables, summary tabulations of the number and percentage within each category (with a category for missing data) of the parameter will be presented. For continuous variables, the mean, median, standard deviation, minimum and maximum values will be given.

Proportions (Survival rate at 1 year, irOR, irDCR, irPFS at 6 mths, OR and DCR) will be presented with exact (Clopper and Pearson) two-sided 95% CI. irOR, irDCR and irPFS are defined according to the irRC; OR and DCR according to RECIST; The date of origin for the survival rate at one year, and irPFS at 6 months is the date of the first ipilimumab dose. Only subjects known to be progression free at 6 months / alive at 1 year will be included in the respective numerators. Any subject receiving at least one dose of ipilimumab will be included in the denominators. The denominator for the irOS and irPFS analyses will be the ITT population. The denominator for the irOR, and irDCR, OR and DCR will be the Response-evaluable population..

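### The HLA-A2 sample may be drawn at any time in the study, while survival by HLA-A2 counts from the first dose, so any late typing raises the absolute rates in both subgroups

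*Protocol*

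**What the plan says.** In the Protocol's Time and Events Schedule the 2 ml EDTA tube is marked in the screening column only. Footnote i then opens the window: "HLA-A2 typing once at the beginning of the study or any other time point of the study". Section 6.5.1 says the same of the blood for HLA typing and SNP analysis, which "will be collected once at the beginning of the study or any other time point of the study". The permission appears twice, so it is not a slip in one footnote. By contrast, footnote n fixes serum and plasma at screening and week 12.

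The tube belongs to the translational programme, which the schedule places under "separate informed consent". HLA type is not known from eligibility: "Enrollment will not be restricted to any specific HLA subtype" (section 1.5).

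The result is used for efficacy. The Synopsis lists as a secondary endpoint "Clinical efficacy parameter (1-year OS, ORR, DCR, PFS at 6 months) according to b-raf mutational status of tumor", continuing to "brain metastases, LDH and HLA-A2". Section 9.5 names the subgroup "HLA-A2 positive versus HLA-A2 negative" among those for which results will be presented. It gives each proportion an exact Clopper-Pearson interval and takes the first ipilimumab dose as the origin for one-year survival and 6-month PFS. The Kaplan-Meier analyses use the same origin. The missing-data category in 9.5 concerns demographic and baseline tables. No untyped group is named for the survival subgroups.

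**The concern.** Membership of an HLA-A2 subgroup depends on a sample that may be taken months after the clock has started. A patient due to be typed late who dies first drops out of the subgroup's denominator and would have counted as a death. A patient who is typed late contributes survival time that was guaranteed before the draw. HLA-A2 is a fixed germline trait, so nobody is put in the wrong group. The timing decides who is classified at all.

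The stake is the absolute rate in each subgroup. The study rationale stresses that the pivotal trial enrolled only HLA-A2-positive patients, so the HLA-A2-negative rate is one of the new things this trial can report. An upward shift in it flatters the drug.

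**Working it through.** **The plan's own figure.** The Synopsis gives a 95% interval of 0.43 to 0.57 for a rate of 0.5 with N=200. Exact Clopper-Pearson for 100/200 is 0.429 to 0.571, so the figure is reproduced. The protocol states no precision for the HLA-A2 subgroups.

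**Direction, without a model.** Let a subgroup have N treated patients, of whom A are alive at one year. If d of the deaths occur before a planned late draw, the reported rate is A/(N−d) instead of A/N. It can only be higher. For 6-month PFS the same holds for draws up to month 6. A later draw also loses some patients who died after month 6, a few of whom may have been progression-free then, so the shift is upward on balance rather than by necessity. Its size was not calculated.

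**Inputs for size.**
- One-year survival 45.6%: Synopsis, Sample Size Justification.
- Draw times of week 12, 24 or 48: the re-staging visits in the schedule.
- Share f of patients left for a late draw: not in the protocol, so assumed at 0%, 10%, 25% and 50%.
- Exponential survival: an assumption.

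**Formula.** The hazard is −ln(0.456)/12 = 0.0654 per month, and S(t) = exp(−0.0654 t). With 84 days = 2.76 months, S is 0.835 at week 12, 0.697 at week 24 and 0.486 at week 48. The share typed is (1−f) + f·S(t), so

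reported rate = 0.456 / [(1−f) + f·S(t)].

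For f = 10% at week 12: 0.456 / (0.90 + 0.10 × 0.835) = 0.456 / 0.9835 = 46.4%.

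| Share late | Week 12 | Week 24 | Week 48 |
|---|---|---|---|
| 0% | 45.6% (0) | 45.6% (0) | 45.6% (0) |
| 10% | 46.4% (+0.8) | 47.0% (+1.4) | 48.1% (+2.5) |
| 25% | 47.6% (+2.0) | 49.3% (+3.7) | 52.3% (+6.7) |
| 50% | 49.7% (+4.1) | 53.7% (+8.1) | 61.4% (+15.8) |

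**Checks.**
- A simulation with f = 25% at week 12, and HLA-A2 unrelated to survival, gave 47.5% in both subgroups against a true 45.6%.
- With a true rate of 0.5 the 25% row becomes +1.9, +3.7 and +6.7.
- This exponential implies a median of 10.6 months against the Synopsis's 10.1. Using 10.1 months for the early deaths gives S = 0.827 at week 12, and 46.4% and 49.9% for f = 10% and 50%, so the result hardly changes.

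**Scale.** An assumed subgroup of 100 at a rate of 0.5 has an exact interval of 0.398 to 0.602, about ±10 points. At low f the bias is well inside sampling error, but averaging over more patients does not remove it.

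**The case against.** The strongest reply is that the schedule marks the tube at screening, and both texts name the start of the study first. If sites follow the mark, nothing is biased. That stands: the bias is conditional on late sampling.

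A reader might infer that both rates are inflated by design, or by 20 points or more. The documents do not support either reading. Late sampling is permitted, not required. A shift of about 22 points needs every patient left until month 6: S is √0.456 = 0.675, and 0.456 divided by 0.675 is 67.5%. That contradicts the screening mark.

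A reader might also infer a formal comparison of the HLA-A2-negative rate with the pivotal trial's 45.6%. None is planned. The protocol itself quotes 45% in section 1.3.6, and 43% for the combined ipilimumab arms in section 9.1.

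Importance is limited too. Section 9.5 calls everything but the primary endpoint exploratory. The Synopsis says only that HLA-A2 results may be presented, and sections 2.2 and 9.3.2 do not list HLA-A2. If late typing is unrelated to HLA type and survival is similar, both groups rise together and their contrast is largely preserved. That does not protect the separate rate and interval that 9.5 gives each group.

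Two features pull the size in opposite directions. The entry criterion of at least six months' expected survival should reduce early deaths. Under the FU-Phase section, patients who progress and are not eligible for re-induction are followed for survival by calls rather than visits, so late blood would come mainly from patients doing well, and the selection would be stronger than calculated.

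Finally, the choice of analysis may belong in a statistical analysis plan. The sampling window does not: it is a protocol rule, and no analysis can recover blood not drawn before death.

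**Conclusion.** The point holds as a conditional bias. The protocol permits HLA-A2 typing after the clock has started, and any patient who dies before a late draw disappears from both subgroups. The absolute one-year survival rates by HLA-A2, as simple proportions and from Kaplan-Meier curves, then come out too high; so, on balance, does 6-month PFS.

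For one-year survival, under an exponential anchored at 45.6%, the bias is zero with full screening sampling. It is about 1 to 2 points if 10% to 20% are typed at week 12 (for 20%: 0.456/0.967 = 47.2%), about 4 points if half are typed at week 12, and about 8 points if half are typed at week 24. The late share is unknown, so no single figure can be claimed. The primary endpoint, in all treated patients, is unaffected. The change is worth making because it costs almost nothing and removes this selection wherever it is followed.

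**What to change.** - In footnote i and in section 6.5.1, strike the alternative that follows the start of the study, from the word *or* onwards. Require the 2 ml EDTA tube before the first dose, with the 20 ml screening blood, in every patient who consents to the translational programme. It cannot be required of patients who withhold that consent.
- Record the date of any sample taken later.
- Base the HLA-A2 one-year survival and 6-month PFS proportions on patients sampled before the first dose. Let late-sampled patients enter only the Kaplan-Meier analysis, at risk from their sample date (delayed entry). Delayed entry does not work for a simple proportion with a Clopper-Pearson interval.
- Report untyped patients and their survival as a separate group. Consent is separate, so there will be some even when the window is closed.

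The cost is one small tube at an existing draw, with no extra visit. A few patients whose screening tube was missed will drop out of the HLA-A2 proportions.
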